For Aim 2, to determine the interaction between outcome expectancy and type of needling delivery/stimulation (EA vs BFA) on pain reduction, we will define response to acupuncture therapy as a continuous outcome measured as percent change of the BPI pain intensity score from baseline to week 12. Similar to our approach in our previous study,^[71]^ we will then build a multiple linear regression model with percent reduction in BPI intensity as the dependent variable, and baseline expectancy and treatment group (EA or SA) as independent variables, including the expectancy and treatment group interaction term. The regression coefficient for the interaction term represents the between-group difference of percent reduction in BPI for one unit change in the expectancy score.

For Aim 3, we hypothesize that those participants with either AA in COMT (rs4680) or GG/AG in TCL1A (rs2369049) will be more likely than those without the genetic combination to respond to acupuncture treatments (EA or BFA). To ensure our findings can result in actionable information to guide clinical care, we will calculate percent pain intensity reduction between Week 12 and Baseline for each patient, and we will define a binary variable for clinical response to acupuncture as 30% pain reduction between week 12 and baseline. This binary response variable is consistent with that established by Farrar et al. to be a clinically important change in pain trials.^[31]^ We will perform rigorous quality control for the genotype data and will exclude genotypes that are missing for >15% subjects and subjects with >15% missing SNPs from subsequent analyses. We will tabulate genotype frequencies and perform tests of Hardy-Weinberg Equilibrium (HWE) separately for each race/ethnicity subgroup. To test our primary hypothesis that polymorphisms in COMT and TCL1A are associated with acupuncture response, we will develop multivariable linear regression models with the genotype for each SNP and treatment indictor (EA vs BFA) included as independent variables. A significant association will be claimed if the *P* value for the genotype variable is <0.025 (since we are testing 2 SNPs). In addition to assessing associations with binary pain response, we will also explore associations with changes in the raw scores and percent change. We will code each genotype as the count of minor alleles in all association testing.

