For Aim 3, we performed a power calculation to compare response to acupuncture in carriers of AA in rs4680 or GG/AG in rs2369049 versus noncarriers in the EA group. In the preliminary study, 47.2% of 38 patients were carriers; the response rates were 45% in noncarriers and ∼78% in carriers.^[54]^ Therefore, assuming 45% carrier rate, there will be 52 carriers (∼45% of 116 patients) and 64 noncarriers. Assuming a 45% response rate in noncarriers, as shown in the preliminary study, we will have at least 90% power at 5% significance level to detect at least 30% difference in response rates between 52 carriers and 64 noncarriers. Similar power calculation applies to comparison of response to acupuncture in carriers and noncarriers in the BFA group.

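### Aim 3 names linear regression for a yes/no response; the test is hardly affected, but effect estimates, intervals and genotype-specific response rates would be better from logistic regression

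*Protocol article*

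**What the plan says.** Protocol article, section 2.14 (Analytic approach), Aim 3, fixes the endpoint first: "we will define a binary variable for clinical response to acupuncture as 30% pain reduction between week 12 and baseline". The hypothesis that COMT and TCL1A polymorphisms are associated with response is then to be tested as follows: "we will develop multivariable linear regression models with the genotype for each SNP and treatment indictor (EA vs BFA) included as independent variables". An association is claimed when the P "value for the genotype variable is <0.025 (since we are testing 2 SNPs"). The continuous versions of the outcome are secondary to this: "In addition to assessing associations with binary pain response, we will also explore associations with changes in the raw scores and percent change". The coding rule is "We will code each genotype as the count of minor alleles in all association testing".

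Section 2.15 (Power analysis and sample size) also treats Aim 3 as a comparison of proportions. It claims "at least 90% power at 5% significance level to detect at least 30% difference in response rates between 52 carriers and 64 noncarriers", and cites preliminary data in which "the response rates were 45% in noncarriers and ∼78% in carriers".

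**The concern.** Ordinary linear regression assumes one residual variance and an unbounded straight line. A yes/no response has variance p(1 − p), which changes with the response rate, and its mean cannot exceed 1. If genotype matters as much as the preliminary data suggest, the model-based standard error is not the correct one, and a straight line in allele count can pass 100% for patients with two minor alleles.

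The text leaves little room to read the linear model as meant for a continuous main outcome. The raw and percent changes are described as additional exploration, and the power statement uses response rates. Aim 2, in the same section, defines response as a continuous percent change and uses linear regression, which fits. Aim 3 changes the endpoint type but keeps the model type.

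What is at stake is the size and precision of the genotype effect and the response rates by genotype. The article says it chose the binary endpoint so that the result could guide care.

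**Working it through.** **Inputs from the article.** Response is 45% in noncarriers and about 78% in carriers; the power statement uses a 30-point difference, so 75%. The carrier rate is 45%, where a carrier has COMT AA or TCL1A GG/AG. Each acupuncture arm has 52 carriers and 64 noncarriers, 116 in all, so 232 over both arms (144 × 0.8 = 115.2 per arm after 20% attrition). The threshold is 0.025 per SNP, taken as two-sided.

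**Assumptions.** Hardy-Weinberg proportions, independent SNPs, and A (COMT) and G (TCL1A) as the counted alleles. With COMT A frequency p and TCL1A G frequency q, a 45% carrier rate requires (1 − p²)(1 − q)² = 0.55. So p = 0.3, 0.4, 0.5 gives q = 0.22, 0.19, 0.14, and q cannot exceed 1 − √0.55 = 0.26.

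**Step 1: the article's power figure.**
- Pooled rate: (52 × 0.75 + 64 × 0.45)/116 = 0.584.
- Null standard error: √[0.584 × 0.416 × (1/52 + 1/64)] = 0.0920.
- Alternative standard error: √(0.1875/52 + 0.2475/64) = 0.0864.
- Power: Φ[(0.30 − 1.96 × 0.0920)/0.0864] = 91.7%, which agrees with the stated minimum of 90%.

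**Step 2: standard error for a carrier split (52 vs 64).** At 78% vs 45% the variances are 0.78 × 0.22 = 0.1716 and 0.45 × 0.55 = 0.2475.
- Linear model: common variance (52 × 0.1716 + 64 × 0.2475)/116 = 0.2135; standard error √[0.2135 × (1/52 + 1/64)] = 0.0863.
- Correct: √(0.1716/52 + 0.2475/64) = 0.0847.
- Ratio 1.019, so 1.9% too wide. At 75% vs 45% it is 0.0877/0.0864, 1.4% too wide.

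**Step 3: standard error for the planned allele-count model.** One SNP per model plus the arm term, with large-sample model-based standard errors compared with sandwich standard errors.

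| COMT A freq. | TCL1A G freq. | Ratio, COMT | Ratio, TCL1A |
|---|---|---|---|
| 0.3 | 0.22 | 1.05 | 1.03 |
| 0.4 | 0.19 | 1.05 | 1.04 |
| 0.5 | 0.14 | 1.04 | 1.07 |
| 0.57 | 0.10 | 1.03 | 1.11 |

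With no genotype effect the ratio is 1.00.

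**Step 4: fitted rates for two-copy patients.** Take p = 0.4, q = 0.19 (0.191 unrounded).
- TCL1A: patients with no G respond at 0.45 + 0.33 × 0.4² = 0.503, others at 0.78, a gap d = 0.277. A carrier effect fitted by a line in allele count gives an expected two-copy fit of 0.503 + d[q² + 2(1 − q)] = 0.503 + 0.277 × 1.654 = 0.96, against a true 0.78. The average fit is just below 100%, so sampling error often carries it over.
- COMT: non-AA patients respond at 0.45 + 0.33 × [1 − (1 − q)²] = 0.564, so d = 0.216. The expected two-copy fit is 0.564 + d(2p − p²) = 0.564 + 0.216 × 0.64 = 0.70.
- Simulation (232 patients, 4,000 runs, p from 0.3 to 0.5): the TCL1A two-copy fit exceeds 100% in about 33–37% of trials when averaged over arms, and in about 43–46% when either arm counts. For COMT it is essentially 0%.
- Few patients are involved: 232 × 0.191² is about 8.

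**Step 5: the test itself.** Simulated rejection under the null at nominal 0.025 is 0.023–0.028 for linear and 0.020–0.027 for logistic regression. For 52 vs 64 at 75% vs 45%, power is 91.5% for both at 0.05, and 87.2% (linear) vs 86.3% (logistic) at 0.025.

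**The case against.** The strongest reply is that nothing the plan decides would change. Its only stated rule is the P < .025 threshold, and Step 5 shows that linear and logistic regression give nearly the same answer. That stands. A second reply is that a linear model on a 0/1 outcome estimates a risk difference, which is the scale of the power statement, so only the variance estimator needs attention. That is fair, and it is why a risk difference with robust errors is an acceptable remedy. A third is that the article does not promise model-predicted rates by genotype. This is also true, so the impossible rates matter only if such fits are reported. Finally, the word linear may be a slip for logistic. The article does not settle this, and a slip would still need correcting.

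A reader might infer that false positives are inflated or that the intervals are too narrow. The article's figures do not support either. The linear standard error is correct when genotype has no effect. It becomes too narrow only in settings such as a carrier-type effect at an allele frequency near 0.5, which fits neither hypothesis: TCL1A cannot exceed about 0.26 under the 45% carrier rate, and the COMT hypothesis concerns the homozygote. A reader might also expect fits above 100% in well over half of trials. With one SNP per model, that requires assigning the whole 45% vs 78% contrast to a single rare SNP, whereas the article gives those rates for carriers of either genotype against carriers of neither.

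**Conclusion.** The mismatch stands as a minor point: a binary endpoint is paired with a linear model, without robust errors or a stated choice of a linear probability model. At the article's own rates the standard errors are about 1–11% too wide, which is conservative. Fitted response passes 100% for two-copy TCL1A patients in about a third to just under half of simulated trials, and essentially never for COMT. Type I error and the P < .025 decision are practically unaffected, so the loss is in estimation and reporting for a tertiary aim. The sizes depend on the assumed allele frequencies, Hardy-Weinberg proportions, independent SNPs, the assumed counted alleles and the preliminary response rates carrying over. Part of the overshoot comes from fitting a carrier effect with an allele count; logistic regression keeps the fit below 100% but does not cure that separate coding question.

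**What to change.** In section 2.14, Aim 3, name logistic regression for the binary 30% response, with the same genotype and arm terms and the same P < .025 threshold. Report odds ratios with confidence intervals and fitted response probabilities by genotype. If a risk difference is preferred, say so and specify robust standard errors; fitted rates can still exceed 100% under that option, so observed rates by genotype should be shown instead. Keep linear regression for the exploratory raw and percent changes.

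The cost is one line of text and no new data. The effect is then reported as an odds ratio unless a risk difference is also derived.

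### Aim 3 hypothesises and powers a composite carrier contrast that no planned test assesses, so the stated 90% power does not describe the planned per-SNP analysis

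*Protocol article*

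**What the plan says.** **Hypothesis (Protocol article, 2.14 Analytic approach, Aim 3).** The hypothesis, about response to either EA or BFA, reads: "those participants with either AA in COMT (rs4680) or GG/AG in TCL1A (rs2369049) will be more likely than those without the genetic combination". This is a single yes/no grouping: homozygous AA at COMT, or at least one G at TCL1A, against neither. For the outcome, "we will define a binary variable for clinical response to acupuncture as 30% pain reduction between week 12 and baseline".

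**Planned test (same section).** The text says "we will develop multivariable linear regression models with the genotype for each SNP and treatment indictor (EA vs BFA) included as independent variables". A SNP is declared associated if its P value is below 0.025, a threshold explained by there being two SNPs. The coding rule is general: "We will code each genotype as the count of minor alleles in all association testing". The same paragraph also words the primary hypothesis more loosely, as an association between polymorphisms in the two genes and response.

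**Power (2.15 Power analysis and sample size, Aim 3).** The calculation is made to "compare response to acupuncture in carriers of AA in rs4680 or GG/AG in rs2369049 versus noncarriers in the EA group". It assumes 45% carriers among 116 patients (52 carriers, 64 noncarriers) and a 45% response rate in noncarriers, and concludes that "we will have at least 90% power at 5% significance level to detect at least 30% difference in response rates". A similar calculation is said to hold for the BFA group.

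**The concern.** The hypothesis and the power statement concern one carrier indicator. The planned test concerns two separate allele counts. They differ in four respects:

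| | Hypothesis and power | Planned test |
|---|---|---|
| Genetic variable | one composite (either genotype) | each SNP on its own |
| Coding | AA only at COMT; GG or AG at TCL1A | 0, 1 or 2 minor alleles |
| Significance level | 5% (power statement) | 2.5% per SNP |
| Patients | one arm in the power statement | both arms, with a modality term |

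Because the coding rule covers every association test, it leaves no room for a carrier-coded analysis elsewhere in the plan. Two things are at stake. The quoted power cannot be relied on for the analysis that will be run. And with two definitions of the predictor in the text, either could be presented as the main one after the data are seen, or a null allele-count result for COMT could be read as refuting the AA hypothesis.

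**Working it through.** **Step 1. Reproduce the stated power.** Inputs from 2.15: n1 = 52, n2 = 64, p2 = 0.45 and a 30-point difference, so p1 = 0.75. Sidedness is not stated and is taken as two-sided.

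- Pooled proportion: (52×0.75 + 64×0.45)/116 = 67.8/116 = 0.5845
- SE under the null: √[0.5845×0.4155×(1/52 + 1/64)] = 0.0920
- SE under the alternative: √[0.75×0.25/52 + 0.45×0.55/64] = 0.0864
- Power at 5%: Φ[(0.30 − 1.960×0.0920)/0.0864] = Φ(1.384) = **91.7%**

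The claim of at least 90% is therefore right for the composite test at 5%.

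**Step 2. Change only the significance level.** At two-sided 2.5%, power is Φ[(0.30 − 2.241×0.0920)/0.0864] = Φ(1.085) = **86.1%**.

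**Step 3. Composite test in both arms.** A modality term can enter the model only if both arms are in it, so n is about 2×116 = 232 (104 carriers, 128 noncarriers). Both standard errors shrink by √2, to 0.0651 and 0.0611. Power at 5% is Φ[(0.30 − 1.960×0.0651)/0.0611] = Φ(2.82), **over 99%**.

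**Step 4. The planned test.** The article gives no allele frequencies, so they are assumed. The COMT A frequency q runs from 0.3 to 0.6. The TCL1A G frequency r is solved from 1 − (1 − q²)(1 − r)² = 0.45 to keep 45% carriers. Hardy-Weinberg equilibrium and independent SNPs are assumed. The truth is 75% response in carriers and 45% in noncarriers. The analysis is a linear regression of 0/1 response on the allele count with a modality term, one SNP at a time, at P<0.025, over 2,000 simulated trials of n = 232. Which allele is counted does not change the test.

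| A frequency | G frequency | COMT | TCL1A | At least one SNP | Composite at 5% |
|---|---|---|---|---|---|
| 0.3 | 0.223 | 11% | 96% | 96% | >99% |
| 0.4 | 0.191 | 27% | 91% | 93% | >99% |
| 0.5 | 0.144 | 54% | 77% | 90% | >99% |
| 0.6 | 0.073 | 87% | 40% | 92% | >99% |

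The simulation standard error near 40% is √(0.4×0.6/2000) = 1.1 points. Repeats move the ends of the ranges by a point or two; 11–86%, 42–96% and 89–96% are used in the summary. Fitting both SNPs jointly gives nearly the same figures.

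**Step 5. Why COMT loses most.** Take q = 0.4, so 16% are AA and 34.5% carry G. Patients with AA respond at 75%. Those without AA respond at 0.345×0.75 + 0.655×0.45 = 55.4%, because some are carriers through TCL1A. The visible COMT contrast is thus about 20 points rather than 30. It also sits in 16% of patients, while the allele count fits a straight line through two genotypes (no A and one A) that do not differ.

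**The case against.** The strongest reply is that the planned analysis keeps a good chance of finding something. In the pooled sample at least one SNP is flagged in about 89–96% of trials under the plan's own effect, which is close to the power quoted. This stands. A reader might infer from the mismatch that Aim 3 is underpowered. The document does not support that, because the low per-SNP figures at n = 116 describe a sample in which the planned model is not run. But flagging one SNP is not a test of the composite, and which SNP is flagged depends on frequencies the article does not give.

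It can also be said that the per-SNP test does address a hypothesis in the text. This stands too. The looser wording in 2.14, and the statements of the aim in the Abstract and Introduction, speak of polymorphisms associated with response. The defect is that there are two wordings: the composite one is powered and the per-SNP one is tested.

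Pooling EA with BFA might be read as a further fault. It is not: the hypothesis concerns response to either modality. Linear rather than logistic regression for a binary response is a minor point at response rates of 45–75%.

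Finally, a full protocol or SAP may exist. That does not remove the point, because the conflict is in the printed text and the coding rule is stated for all association tests.

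**Conclusion.** The concern holds in a limited form. The composite carrier hypothesis has no planned test, and the 90% power statement describes an analysis the plan does not contain. The 90% is not an arithmetic error.

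The consequence is uneven. Overall power to flag some association is probably adequate in the pooled sample. Power for COMT alone could be anywhere from about 11% to 86%, and for TCL1A from about 42% to 96%. These per-SNP figures rest on the assumed allele frequencies, a 45% carrier rate, the 75% vs 45% response rates, independent SNPs and two-sided tests. If the levels were meant as one-sided, the composite at n = 116 would have 95.7% at 5% and 91.7% at 2.5%, but the mismatch in predictor and coding would remain.

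Aim 3 is tertiary and touches neither the primary endpoint nor the gatekeeping procedure. This should be fixed before analysis, but it does not threaten the trial's main conclusions.

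**What to change.** Choose one of two coherent routes and state it before the genotype data are analysed.

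1. **Test the composite.** Make the pre-defined carrier indicator (AA at rs4680, or GG/AG at rs2369049) the main Aim 3 test of 30% response at 5%, with EA and BFA pooled and a modality term. Keep the per-SNP tests at 2.5% as secondary, limit the minor-allele-count rule to those tests, and restate the power for the pooled composite test (over 99% under the present assumptions).
2. **Test the SNPs.** Restate the hypothesis separately for each SNP and recompute power for the allele-count tests at 0.025 in the pooled sample, giving the allele frequencies assumed.

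Route 1 follows the stated hypothesis most closely. Route 2 is equally valid if the sponsor prefers not to rest the main test on a grouping taken from a preliminary study of 38 patients. Either route costs a few sentences in 2.14 and one recalculated power statement in 2.15, with no new data, samples or genotyping.

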### Power analysis and sample size

2.15

For our Aim 1 sample size/power considerations for comparisons between EA versus WLC and BFA versus WLC, we calculated the smallest standardized effect size (ie, Cohen d) that we will be able to detect with 80% power, given our gatekeeping multiple testing strategy and sample sizes of 144 in each of the acupuncture arms and 72 in WLC. To estimate this smallest detectable effect size, we applied sample size calculations designed for LMMs in the context of RCTs with participant attrition.^[72]^ Using the “power.mmrm” function from the R package “longpower,” we applied the formulas in Lu et al^[72]^ to derive the smallest detectable effect size for the coefficient of the time-by-arm interaction term in our LMM (see Section 2.14), which we transformed to represent the standardized mean difference (ie, Cohen d) between 2 arms in changes in pain intensity from baseline to week 12. Assuming a 20% attrition rate across all arms by week 12, significance threshold of *P* < 0.025, a correlation between baseline and post-treatment assessments of 0.5, and power of 80%, we will be able to detect an effect size of ≥0.48 between either EA versus WLC or BFA versus WLC. This is a moderate effect size which is smaller than that found in our previous pilot trial^[65]^ (effect size of 0.76) and that detected by the meta-analysis conducted by Vickers et al (0.5 between acupuncture and standard care).^[17]^ Thus, our trial is adequately powered to detect such a difference.

As part of our gatekeeping multiple testing procedure, we split our overall type I error rate of 5% evenly between the test of EA versus WLC and the test of BFA versus WLC. If neither, or only one of, EA or BFA is better than WLC at the *P* < .025 threshold, then there is no need for us to evaluate whether BFA is noninferior to EA. On the contrary, if both EA and BFA have significant improvements in pain intensity compared to WLC at the *P* < .025 threshold, then we will proceed to evaluate whether BFA is noninferior to EA. In this gatekeeping scenario, the alphas from both of the comparisons with WLC will propogate to our noninferiority comparison and our overall type I error rate for testing our primary endpoint will be preserved at 5%. Given our sample size, we will have 80% power to find BFA non-inferior to EA with respect to change in BPI pain intensity within a margin of .33 change-score standard deviations (SDs), assuming a 1-sided significance threshold of *P* < .05. We expect this SD to be between 2 and 3, so this margin translates to between 0.67- and 1-point difference in BPI pain intensity reduction. If we are able to demonstrate this, the interpretation would be that BFA is as good as EA with the caveat that we cannot exclude the possibility that EA is slightly better but not to the degree of clinical importance.

Aim 2 hypothesizes that there is a significant interaction between treatment and baseline AES on percent pain intensity reduction. Our preliminary data demonstrate that the regression coefficient for the interaction term between treatment and AES is 8.31 (standard error = 4.21) using percent change in BPI-severity as the dependent variable in a linear regression model including treatment, baseline AES, and their interaction.^[71]^ Using a conservative estimate of correlation (0.2) between the interaction term and the dependent variable, we need a total of 191 subjects to detect this observed interaction effect with 80% power. Thus, our proposed sample size (288 subjects in both EA and BFA groups) is sufficient to detect this observed interaction effect.

For Aim 3, we performed a power calculation to compare response to acupuncture in carriers of AA in rs4680 or GG/AG in rs2369049 versus noncarriers in the EA group. In the preliminary study, 47.2% of 38 patients were carriers; the response rates were 45% in noncarriers and ∼78% in carriers.^[54]^ Therefore, assuming 45% carrier rate, there will be 52 carriers (∼45% of 116 patients) and 64 noncarriers. Assuming a 45% response rate in noncarriers, as shown in the preliminary study, we will have at least 90% power at 5% significance level to detect at least 30% difference in response rates between 52 carriers and 64 noncarriers. Similar power calculation applies to comparison of response to acupuncture in carriers and noncarriers in the BFA group.

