### Randomization

2.5

We will randomize 360 participants using MSK's Clinical Research Database, a secure system that provides full allocation concealment and ensures that treatment group assignments cannot be guessed before or modified after a patient is enrolled in the trial. Group assignment (2:2:1 for EA:BFA:WLC) will be performed using permuted block randomization, stratified by accrual site (main campus vs regional sites) and baseline opioid use (yes vs no). The study statisticians will be blinded to treatment assignments.

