### Analytic approach

2.14

We will perform analysis according to the intention-to-treat (ITT) principle (ie, subjects will be analyzed according to the treatment group to which they were randomly allocated). The change in BPI pain intensity from baseline to Week 12 is the primary endpoint for this study. To maintain the overall type 1 error level at 5% for testing the primary endpoint between study arms, we will use a “gatekeeping” approach to manage the multiple statistical comparisons.^[68]^ We will first separately compare BFA to WLC and EA to WLC using the methods described below. If both acupuncture groups are significantly superior to WLC at significance threshold *P* < .025 (to maintain overall type 1 error at 5% for the 2 tests), we will compare BFA to EA using a noninferiority approach, calculating a 1-sided, 95% confidence interval.

For Aim 1, to compare the effects of acupuncture on patient-reported pain (primary outcome), physical functions, and comorbid symptoms (fatigue, sleep disturbance, anxiety, depression, and PTSD) at week 12, we will use linear mixed models (LMMs)^[69]^ to test differences between treatment arms in score changes from baseline to week 12, with randomization strata as covariates. Specifically, in addition to the randomization strata, the models will adjust for baseline score^[70]^ and will contain assessment time, treatment arm, and the time-by-treatment arm interaction. The interaction term will be used to test whether the treatment arms significantly differ in their changes from baseline. To determine the durability of treatment effects, we will report the change between week 12 and week 24 using ordinary least squares regression in the BFA and EA group separately. For secondary outcomes, we will use similar analytical strategies for physical functions, co-morbid symptoms (fatigue, sleep disturbance, anxiety/depression, PTSD), and quality of life. Additionally, we will use the weekly pain medication diaries to calculate average pain medication usage across the study time for each study participant to determine if acupuncture decreased the use of pain medication.

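### Holding both wait-list comparisons to P<.025 before the BFA–EA noninferiority test is valid but needlessly strict; Holm gains power at the same 5% error rate

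*Protocol article*

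**What the plan says.** The Analytic approach section (2.14) compares BFA with WLC and EA with WLC separately. The third comparison is conditional: "If both acupuncture groups are significantly superior to WLC at significance threshold" P<.025, BFA is then compared with EA for noninferiority using a one-sided 95% confidence interval.

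The Power analysis and sample size section (2.15) repeats the rule. The 5% is divided equally: "we split our overall type I error rate of 5% evenly between the test of EA versus WLC and the test of BFA", with the wait list as comparator in both. When only one comparison succeeds, or none does, "then there is no need for us to evaluate whether BFA is noninferior to EA". If both succeed, "the alphas from both of the comparisons with WLC will propogate to our noninferiority comparison", which is run at one-sided .05.

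The same section gives power step by step. For each WLC comparison it gives 80% power at an effect of 0.48, with "sample sizes of 144 in each of the acupuncture arms and 72 in WLC" and 20% attrition. For the third test it says: "Given our sample size, we will have 80% power to find BFA non-inferior to EA with respect to change in BPI pain intensity", with a margin of 0.33 change-score SDs. It gives no probability that both WLC comparisons succeed, and none that the full sequence ends in a noninferiority claim.

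**The concern.** The plan already passes alpha forward from rejected hypotheses, but only to the third test. Once one WLC comparison is rejected at .025, its share of the 5% is idle while the other comparison is still held to .025. Suppose one arm has P<.025 and the other has a P between .025 and .05. The plan then gives up a superiority claim for the second arm that a 5% procedure would support. It also does not run the formal noninferiority test.

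The second issue is how the noninferiority power reads. That test is reached only after two comparisons that share a 72-patient control arm and are each sized for about 80% power. A reader who takes 80% as the chance of a noninferiority conclusion would be too optimistic unless the acupuncture effect is well above the sizing effect. The BFA–EA question matters to the trial's rationale, because the Discussion stresses that BFA is easier to deliver and scale.

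**Working it through.** **Inputs.** From section 2.15: 144/144/72 patients; 20% attrition by week 12; baseline-to-follow-up correlation 0.5; P<.025 for each WLC comparison; detectable effect 0.48 at 80% power; noninferiority margin 0.33 SD at one-sided .05; reference effects 0.5 (meta-analysis) and 0.76 (pilot). The 2:2:1 allocation is in section 2.5.

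**Assumptions.** The article does not give the sidedness of the WLC tests; two-sided reproduces its figure. It states no true EA–BFA difference; zero is assumed. The 0.60 SD row below is an illustrative value. Normal approximations are used throughout.

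**1. Variance under attrition.** With correlation 0.5 the change-score SD is √(2 − 2×0.5) = 1, so raw-score and change-score SD units coincide. Two variance factors bracket the analysis:
- Mixed model using all data: average information per patient is 0.8·R⁻¹ + 0.2·diag(1, 0), where R has off-diagonal 0.5. Its inverse has entries 1, 0.5 and 1.1875, so the change has variance 1 + 1.1875 − 2×0.5 = 1.1875.
- Completers only: 1/0.8 = 1.25.

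**2. Reproducing the plan's figures.**
- WLC comparisons: d = (2.241 + 0.842) × √[1.1875 × (1/144 + 1/72)] = 3.083 × 0.1573 = 0.485. With assessments at weeks 0, 4, 10 and 12 it is 0.481, and for completers only 0.498. The stated 0.48 is reproduced.
- Noninferiority, completers: SE = √(1.25 × 2/144) = 0.1318; power = Φ(0.33/0.1318 − 1.645) = Φ(0.86) = 80.5%. With factor 1.1875 it is 82.2%. The stated 80% is therefore the power of this test alone.

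**3. Error control with Holm followed by noninferiority.**
- Both WLC nulls true: any false claim needs the smaller P<.025, which has probability at most 2 × .025 = 5%.
- One WLC null true: rejecting it needs its own P<.05. A false noninferiority claim also needs that rejection first. The total is at most 5%.
- Neither WLC null true: the only possible error is a false noninferiority claim, tested at one-sided .05.

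Simulation over six sets of true effects gave a highest familywise error of 5.0% under either rule. Any result with both P<.025, or with a single P<.025, leads to the same claims under Holm, so nothing is lost.

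**4. Probability of completing the sequence.** I simulated the three arm means (4 million draws) with both arms at the same true effect. The shared control gives the two WLC tests a correlation of (1/72)/(1/144 + 1/72) = 2/3. Ranges run from factor 1.25 to factor 1.1875.

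| True effect (SD) | Rule | Power per WLC comparison | Both comparisons succeed | Noninferiority claimed |
|---|---|---|---|---|
| 0.48 | current | 76.8–79.1% | 66.8–69.7% | 55.7–59.2% |
| 0.48 | Holm | 81.3–83.4% | 75.7–78.2% | 62.4–65.7% |
| 0.50 | current | 80.4–82.6% | 71.4–74.2% | 59.3–62.8% |
| 0.50 | Holm | 84.6–86.5% | 79.6–82.0% | 65.5–68.7% |
| 0.60 | current | 93.0–94.2% | 88.8–90.6% | 72.6–75.5% |
| 0.60 | Holm | 95.2–96.1% | 93.1–94.4% | 75.6–78.2% |
| 0.76 | current | 99.3–99.5% | 98.8–99.1% | 79.7–81.7% |
| 0.76 | Holm | 99.6–99.8% | 99.4–99.6% | 80.1–82.0% |

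At 0.48 SD, noninferiority power given that both WLC comparisons have succeeded is 83–85% under the current rule.

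**The case against.** An even split with a prespecified order of testing is a standard, valid procedure, and the article's statement that the overall error is preserved at 5% is correct. On this view Holm is only a preference. That does not fully answer the point. Holm keeps every claim the current rule makes and adds others at the same error rate, so it is a specific gain and not a matter of taste.

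Other parts of the objection stand:

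- **The 80% is not misquoted.** It comes directly after the text on the case where both comparisons succeed, and it carries its own margin and threshold. Read as stand-alone power (80.5–82%) or as conditional power (83–85% at 0.48 SD), it is accurate or slightly conservative. A reader might infer an 80% overall chance of a noninferiority claim, but the article does not say so.
- **56–59% is one scenario.** It needs both arms to sit at the smallest detectable effect with EA equal to BFA. Section 2.15 also cites 0.5 and 0.76, where the current rule gives 59–63% and 80–82%.
- **A failed first stage does not remove the EA–BFA comparison.** It stops only the formal noninferiority test. The mixed model contains all three arms, so a difference with its interval can still be estimated, and Aim 2 sets EA against BFA by expectancy regardless.
- **Timing matters.** Enrollment began in March 2017 and assessments were due to finish in May 2020. Relaxing a published primary testing rule late in a trial without a sham control can look self-serving, even though section 2.5 blinds the statisticians.

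**Conclusion.** The entry rule for the noninferiority test is valid but stricter than 5% familywise control requires. At 0.48 SD in both arms with EA equal to BFA, Holm would raise the chance that both WLC comparisons succeed by about 9 points and the chance of a noninferiority claim by about 6 to 7 points. The second gain shrinks to about 3 points at 0.60 SD and to less than 1 point at 0.76 SD. Holm does not bring the full sequence to 80% at 0.48 or 0.50 SD.

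Two stronger readings are not supported: that type I error is inflated, and that the stated noninferiority power is wrong. What remains on power is a labelling point. The 80% describes one test, and the probability of completing the sequence depends on the true effect and is not given. All sequence figures assume two-sided WLC tests, equal true effects in the two acupuncture arms, and 20% attrition handled as in section 2.15.

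**What to change.** Replace the entry rule in sections 2.14 and 2.15 with Holm:

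1. Compare the smaller of the two WLC P values with .025. If it fails, stop.
2. If it passes, compare the larger with .05.
3. If both are rejected in favour of acupuncture, test BFA against EA for noninferiority at one-sided .05, with the margin unchanged.

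State whether the WLC tests are two-sided.

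In section 2.15, label the 80% as the power of the noninferiority test alone. Beside it give the probability of passing both WLC comparisons and the margin. If the current rule is kept, that is about 56–59% at 0.48 SD, 59–63% at 0.50 SD and 80–82% at 0.76 SD, assuming EA equals BFA. If Holm is adopted, it is 62–66%, 65–69% and 80–82%.

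The sample size does not change. The cost is a dated, justified change to a published primary testing rule, made before unblinding, and a less favourable power statement at the smaller effects. If it is too late for a credible rule change, the relabelling can be done on its own.
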